## Study area and population surveyed

The study will be carried out on Unguja, the main island of the Zanzibar archipelago belonging to the United Republic of Tanzania. The island is ~87 km long with a surface area of ~1660 km2. The Zanzibar archipelago has a relatively high precipitation with a mean annual rainfall of 1955 mm with heaviest rains occurring in March-May. The average annual temperature ranges from 23°C to 28°C. The population of Unguja (623,000 inhabitants in 2002) is mainly settled in the densely populated West of the island. Zanzibar’s major economic sectors are based on agriculture, trade, industries and tourism.

The schools of Kinyasini and Chaani, located in the North district of Unguja, are selected for this study. Selection criteria included:

1. high prevalences of soil-transmitted helminths (*T. trichiura*:42.9%; hookworm: 22.5%; *A. lumbricoides*: 16.5%) were revealed in children visiting these schools in a study in 2007;
2. a high number of participants (94%) submitted at least 1 stool sample for examinations in a study in 2007;
3. the schools are regularly visited by members of the HCLU for annual screenings and subsequent treatment of the schoolchildren in the frame of the national helminth control programme; hence, the children and teachers are familiar with the team and facilitate study procedures; and
4. the schools are about 40 km out of Zanzibar Town and easily accessible by project vehicles on tamarack roads, guaranteeing a fast transfer of equipment to the school and of stool samples back to the HCLU.
5. 500-2000 children are visiting each of the two schools and thus the calculated sample size of 2000 children to include in the study will be available.
6. both schools can provide empty classrooms that will serve for collection of stool containers without disturbing teaching; these empty rooms will also serve for treatment and observation of acute adverse events for one hour after treatment and for medical consultation in privacy on the day of treatment.

# Patient inclusion and exclusion and withdrawal criteria

## Patient inclusion criteria

1. Age ≥5 years, both sexes.
2. Submission of 1 stool sample of sufficient size to perform a total of 2 thick Kato-Katz smears at the baseline parasitological survey.
3. Submission of 1 stool sample of sufficient size to perform a total of 2 thick Kato-Katz smears at the day of treatment.
4. Infection with *T. trichiura* as determined with the Kato-Katz method at the baseline survey. Additionally, also children with *A. lumbricoides* and/or hookworm infections will be included in one of the 4 treatment arms.
5. For females, not pregnant, as verbally assessed by medical personnel on the day of treatment.
6. Absence of major systemic illnesses, as assessed by medical personnel on the day of treatment.
7. No anthelminthic treatment in the past 4 weeks, as verbally confirmed by the participant at the baseline survey.
8. Written informed consent by the parent/legal guardian.

## Patient exclusion criteria

1. No stool sample given at baseline survey or day of treatment.
2. No infection with *T. trichiura*, *A. lumbricoides* and/or hookworm at baseline
3. Subjects with fever or other signs of acute illness.
4. Subjects with severe neurological disorder.
5. Subjects with severe liver disorder, as assessed by medical personal with an abdominal examination on the day of treatment.
6. Pregnant schoolgirls.
7. Recent history of anthelminthic treatment.
8. Consent not given.

## Patient discontinuation and withdrawal criteria

Apart from falling under the exclusion criteria the children’s participation in this research study is entirely voluntary. The children may choose not to participate and withdraw their/their parents’ consent of participation at any time. The children will not be penalized in any way if they decide not to participate or to withdraw from this study.

# Study and treatment protocol

## Field procedures

The headmasters of the schools will be informed about the purpose and procedures of the study. Once informed consent is obtained, the objectives and procedures will be explained to the teachers, schoolchildren and their parents and written informed consent (see Appendix 1) by the participants’ parents/legal guardians will be obtained.

Field procedures are as follows. The study will be conducted between March and May 2009 (for exact protocol see Appendix 2). In an in-depth baseline survey before treatment, approximately 2000 children will be asked to submit 1 stool sample of sufficient size (at least 5 g) to perform the anticipated examinations. On the first day of the survey, about 200 participants will be given a plastic container and invited to bring a fresh stool specimen the following morning. Upon collection, a unique identification number will be attached to the container and demographic data will be collected (e.g., age and sex).

This procedure will be repeated over several days, entering ~200 additional schoolchildren every day up to a total of 2000 children. One of the inclusion criteria for the randomized drug trial is an infection with *T. trichiura* (see point 5.). We anticipate that with an expected prevalence of 25% of *T. trichiura* infections and with a compliance of 95% working for 2-3 weeks in Kinyasini and Chaani schools will suffice to obtain the required sample size of at least 540 children infected with *T. trichiura*. In addition those children diagnosed with *A. lumbricoides* and/or hookworm will also be attributed to one of the 4 treatment regimens, but their numbers are not included into the sample size calculations. Before the onset of the trial, each individual included into the trial will be physically examined by a medical assistant for exclusion criteria.

Once all samples have been collected and analysed, a randomized treatment list allocating the IDs of the ~540 children infected with *T. trichiura* and of the remaining children infected with *A. lumbricoides* and/or hookworm to one of the 4 treatment regimens will be prepared. On the day before treatment the selected children will be given another stool container and they will be asked to provide another stool sample the following morning. On the day of treatment the stool samples will be collected and all children’s weights will be recorded. The children will be allocated to one of four groups, as follows:

1. Single-dose albendazole group; children will receive one tablet of albendazole (400 mg) and a placebo resembling ivermectin (number of tablet according to weight).
2. Mebendazole group; children will receive a single dose of mebendazole (500 mg) and a placebo resembling ivermectin (number of tablet according to weight).
3. Albendazole plus ivermectin group; children will receive one tablet of albendazole (400 mg) plus ivermectin tablets according to their weight (200 µg/kg).
4. Mebendazole plus ivermectin group; children will receive one tablet of mebendazole (500 mg) plus ivermectin tablets according to their weight (200 µg/kg).

The participants will be asked to swallow the drugs with clean water and the health worker administering the drugs will check that the tablets have been swallowed by looking into the mouth and under the tongue. During the entire treatment phase and for one additional hour, a clinician will be present for supervising drug intake, monitoring and registering acute adverse events of the four drug regimens and to provide medical assistance where necessary. The medical assistant will be provided with a complete list of possible adverse events of the respective drug. In case of adverse events, appropriate medical action will be taken, e.g. administration of drugs for relief.

The children will be kept under medical supervision for one hour after treatment. The staff of the Public Health Centres (PHC) located nearest to the two schools (Upenja and Chaani) will be informed and undergo a pharmacovigilance training in the week before treatment. Additionally, the PHCs will be provided with first aid drugs and will remain open for 24 hours on the day of treatment. Children, parents and teacher will be informed that in case of any adverse reaction they can refer cases to the PHC at day and night time for 24 hours. Forty eight hours after treatment, solicited adverse events due to the treatment will be assessed by a previously tested questionnaire (see Appendix 3). The onset and duration of the side effects will be recorded and graded as follows:

- *mild:* present but not requiring any interference;
- *moderate:* (1) present and requiring medication for symptomatic relief as requested by the affected people or (2) present and interfering with normal daily activities; and
- *severe:* present and required medical intervention beyond symptomatic relief.

Three to four weeks after drug administration, treated children will be given a follow-up stool container and asked to bring a fresh stool specimen the following morning for a follow up of the treatment. Upon collection of this container the children will be handed out another container and invited to bring a second stool sample the next morning.

In the last week of the study all infected study participants will be treated free of charge with the current drug of choice albendazole (400 mg) against *A.* *lumbricoides*, *T.* *trichiura* and hookworm. The subjects infected with any soil-transmitted helminth but falling under the exclusion criteria (no. 4 and 7) will be offered a treatment after termination of their illness or after pregnancy.

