# Sample size

Sample size calculations are based on the differences in CR of albendazole or mebendazole versus albendazole and ivermectin against *T. trichiura*.

The CRs of treatment with albendazole (400 mg single oral dose) and mebendazole (500 mg single oral dose) have been reported in a recent meta-analysis to be 28% (95% CI, 13%-39%) and 36% (95% CI, 16%-51%) for *T. trichiura*; 88% (95% CI, 79%-93%) and 95% (95% CI, 91%-97%) for *A. lumbricoides*; and 72% (95% CI, 59%-81%) and 15% (95% CI, 1%-27%) for hookworm infections *(*34).

The CR of the combination treatment of albendazole (400 mg single oral dose) plus ivermectin (200-400 µg/kg) as single therapy were reported from Haiti and the Philippines for the major soil-transmitted helminths and indicated to be 79.6% and 65.1%, respectively for *T. trichiura*, 100% and 78.1%, respectively for *A. lumbricoides* and 100% for hookworm infections *(38,* 55).

No relevant references on a combination therapy of mebendazole and ivermectin exist according to a recent review on the efficacy and safety of drug combinations *(*35).

Information about CR and ERR of albendazole, mebendazole and ivermectin are also available for Zanzibar. The CRs of a single dose of albendazole (400 mg) and mebendazole (500 mg) were assessed in a single-blind randomized controlled trial performed in Pemba, Zanzibar, in 1992/93 and were 10.5% and 14.2% for *T. trichiura*, 98.9% and 97.8% for *A. lumbricoides* infections and 56.8% and 22.4% for hookworm *(*51). ERRs for albendazole and mebendazole in the same study were 73.3% and 81.6% for *T. trichiura*, 99.6% and 99.3% for *A. lumbricoides* infections and 97.7% and 82.4% for hookworm *(*51).

The CR and ERR of a single dose ivermectin (200 µg/kg) were assessed in Unguja in 1994 and were 11.3% and 58.9% for *T. trichiura*, 100% and 100% for *A. lumbricoides* infections and 0% and 0% for hookworm *(*18).

The sample sizes indicated in **Table 1** were calculated in Microsoft Excel with an equation given by Fleiss *(*56):

7.85*((A1*(1-A1))+(B1*(1-B1)))/(ABS(A1-B1))^2+2/ABS(A1-B1)+2

Where A1 is the estimated CR from treatment A (e.g. albendazole or mebendazole) and B1 is the estimated CR from treatment B (e.g. albendazole plus ivermectin or mebendazole plus ivermectin).

Using a significance level of 5% to detect greater efficacy of one treatment, and a power of 80%, the following table indicates the required number of individuals **per treatment group** at different CRs:

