**Table 1: Cure rates for *T. trichiura***

**Treatment A (albendazole or mebendazole)**

| **Treatment B**  **(albendazole or mebendazole plus ivermectin)** | 15% | 20% | 30% | 35% | 40% | 45% | 50% | 55% |
| --- | --- | --- | --- | --- | --- | --- | --- | --- |
| 60% | 21 | 27 | 48 | 69 | 106 | 185 | 407 | 1573 |
| 65% | 17 | 21 | 36 | 48 | 69 | 105 | 182 | 395 |
| 70% | 14 | 18 | 28 | 36 | 48 | 67 | 102 | 175 |
| 75% | 12 | 15 | 22 | 27 | 35 | 47 | 65 | 97 |
| 80% | 10 | 12 | 18 | 21 | 27 | 34 | 44 | 61 |
| 85% | 9 | 10 | 14 | 17 | 21 | 25 | 32 | 41 |
| 90% | 8 | 9 | 12 | 14 | 16 | 20 | 24 | 29 |

Based on the given information we estimate the CR of albendazole/mebendazole for *T. trichiura* infections to be between 20% and 45% and the CR of the combination of albendazole/mebendazole plus ivermectin to be between 65% and 80%. Hence, a sample size of at least 105 participants per treatment group is needed for significance analysis.

In the proposed study sites, the prevalence of *T. trichiura* infections is most likely to be above 30% and the compliance is estimated to be around 90%. These assumptions are based on a study performed in Kinyasini and Chaani schools in 2007 where 25.9% of the children were found to be infected with *T. trichiura* after examination of 1 stool sample and 47.9% after examination of 3 stool samples with the Kato-Katz method and where the compliance to submit 1-3 stool samples was >85%. In view of the required number of cases per group, and allocating for patients lost to follow-up, at least 2000 subjects would have to be screened so that 500-600 infected individuals infected with *T. trichiura* can enter the trial (see Appendix 5).

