**Week 2 to 5**

- Collect filled stool containers from 1st 200 pupils and record them on the form

- Hand out labelled stool collection containers to 2nd 200 participants

- Transport collected full stool containers to the laboratory

- Prepare 2 Kato-Katz slides from each stool sample as described beyond

- Preserve 1 g of stool in SAF from ~250 randomly selected children

 Repeat the procedure until 500-600 children infected with *T. trichiura* are identified (approximately when stool samples of 2000 children are examined)

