**Appendix 8: Flowchart of participants infected with *T. trichiura* and included in the RCT**

Baseline screening of pupils from Kinyasini school

(n = 1800)

Children infected with *T. trichiura*

Random allocation to **4** treatment groups

(n = 540)

Children **not** infected with *T. trichiura*

(expected **prevalence 30%;** n = 1260)

Children falling under **exclusion** criteria

(5%; n = 7)

Albendazole

(n = 135)

Albendazole and Ivermectin

(n = 135)

Mebendazole

(n = 135)

Cure rate?

Egg reduction rate?

(n = 103)

Cure rate?

Egg reduction rate?

(n = 103)

Cure rate?

Egg reduction rate?

(n = 103)

Participants **not** complying

(10%; n = 14)

Albendazole treatment

(n = 114)

ALB + IVM treatment

(n = 114)

Mebendazole treatment

(n = 114)

Children falling under **exclusion** criteria

(5%; n = 7)

Participants **not** complying

(10%; n = 14)

Children falling under **exclusion** criteria

(5%; n = 7)

Participants **not** complying

(10%; n = 14)

Random selection of pupils from Chaani and Kinyasini school

(n = 2000)

Children **not** complying

(expected non-compliance of 10%; n = 100)

Participants **not** complying

(10%; n = 11)

Participants **not** complying

(10%; n = 11)

Participants **not** complying

(10%; n = 11)

Mebendazole and Ivermectin

(n = 135)

Participants **not** complying

(10%; n = 14)

Children falling under **exclusion** criteria

(5%; n = 7)

MEB + IVM treatment

(n = 114)

Participants **not** complying

(10%; n = 11)

Cure rate?

Egg reduction rate?

(n = 103)

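### The screening figures do not produce the stated sample size: the Field procedures inputs give 475 infected children, not 540, and the flowchart's favourable case ends at 103 evaluable per arm against a requirement of 105

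*Combined protocol and SAP*

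**What the plan says.** **Requirement.** The Sample size section sets the error rates: "Using a significance level of 5% to detect greater efficacy of one treatment, and a power of 80"%. It uses the equation "7.85*((A1*(1-A1))+(B1*(1-B1)))/(ABS(A1-B1))^2+2/ABS(A1-B1)+2". Below Table 1, the single-drug cure rate for *T. trichiura* is assumed "to be between 20% and 45% and the CR of the combination of albendazole/mebendazole plus ivermectin to be between 65% and 80"%, and the conclusion is that "a sample size of at least 105 participants per treatment group is needed for significance analysis".

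**Yield, Field procedures.** Children are entered at about 200 a day up to 2000. Prevalence of 25% and compliance of 95% "will suffice to obtain the required sample size of at least 540 children infected with" *T. trichiura*.

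**Yield, Sample size.** Prevalence is taken as above 30% and compliance as about 90%. The supporting evidence is a 2007 survey of the same schools, in which "25.9% of the children were found to be infected with" *T. trichiura* on one stool sample and 47.9% on three, with compliance above 85% for giving one to three samples. At least 2000 are to be screened so that 500–600 infected children enter.

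**Yield, Appendix 3 (Week 2 to 5).** Screening is repeated until 500–600 infected children are found, "approximately when stool samples of 2000 children are examined".

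**Yield, Appendix 8 flowchart.** From 2000 selected, the first loss is printed as "expected non-compliance of 10%; n = 100", yet 1800 are screened. At 30% prevalence, 540 are allocated, 135 per arm. Each arm loses 7 (5%) and 14 (10%) before treatment and 11 (10%) at follow-up, which leaves 103.

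**The concern.** The requirement of 105 and the recruitment figures meant to deliver it stand in four places and do not agree. One section's inputs do not give the total it states. Another replaces those inputs with more favourable ones that its one-sample evidence does not clearly support, and eligibility rests on one baseline stool sample. The flowchart, on the favourable inputs, still finishes below 105. A reader cannot tell which prevalence, compliance, screening limit or stopping point governs.

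At stake is whether the cure-rate comparison against *T. trichiura* has its stated power at the contrast used to size it. The evaluable count is the right one to compare with 105, because Study type and measurement computes the cure rate in children with stool samples from both day 0 and follow-up.

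**Working it through.** **1. The plan's requirement reproduces.** At 45% vs 65%: 7.85 × (0.45 × 0.55 + 0.65 × 0.35) / 0.20² + 2/0.20 + 2 = 7.85 × 0.475/0.04 + 12 = 105.2. Table 1 prints 105; rounding up gives 106. The constant 7.85 is (1.960 + 0.842)², that is, two-sided 5% and 80% power. All 56 cells of Table 1 reproduce to within 1.

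**2. The flowchart reproduces, apart from one entry.** 2000 × 0.90 × 0.30 = 540, and 540/4 = 135. Then 135 − 7 − 14 = 114, and 114 − 11 = 103. Ten per cent of 2000 is 200, which is what leaves 1800; the printed 100 is wrong.

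**3. Infected children found when 2000 are approached, and evaluable per arm** (infected/4 × 0.85 × 0.90, the flowchart's losses):

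| Source of inputs | Compliance × prevalence | Infected | Evaluable per arm |
|---|---|---|---|
| Field procedures | 95% × 25% | 475 | 91 |
| Sample size compliance, one-sample prevalence | 90% × 25.9% | 466 | 89 |
| 94% giving at least one sample in 2007 (Study area), one-sample prevalence | 94% × 25.9% | 487 | 93 |
| Flowchart | 90% × 30% | 540 | 103 |
| Lower end of the stopping range | – | 500 | 96 |
| Upper end of the stopping range | – | 600 | 115 |

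On the Field procedures inputs, 540 infected would need 540/(0.95 × 0.25) = 2274 children.

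**4. Power at 45% vs 65%.** Inverting the plan's equation gives power = Φ(√((n − 12) × 0.04/0.475) − 1.96). Dropping the two correction terms replaces n − 12 by n.

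| n per arm | Plan's formula | Without correction terms |
|---|---|---|
| 89 | 72% | 78% |
| 91 | 73% | 79% |
| 93 | 74% | 80% |
| 96 | 76% | 81% |
| 103 | 79% | 84% |
| 115 | 84% | 88% |

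**5. Power elsewhere in the assumed range.** Table 1 has 20 cells with single-drug cure of 20–45% and combination cure of 65–80%. Only 45% vs 65% needs 105; the other 19 need 69 or fewer. The two neighbouring cells at 89 per arm, where 2/0.25 + 2 = 10:
- 40% vs 65%: Φ(√(79 × 0.0625/0.4675) − 1.96) = 90%.
- 45% vs 70%: Φ(√(79 × 0.0625/0.4575) − 1.96) = 91%.

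Close to the corner, 91 per arm keeps 80% power at 45% vs 66.6%: 7.85 × (0.2475 + 0.2224)/0.216² + 2/0.216 + 2 = 90.3. The detectable difference there grows from 20 to about 21.6 points.

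**6. What the requirement implies for screening.** For 105 evaluable: 105 × 4/(0.85 × 0.90) = 549 infected. For 106: 106/0.765 = 138.6, so 139 per arm and 556 infected. Children to approach:
- 25% and 95%: 2312 (for 549) to 2341 (for 556).
- 25.9% and 90%: 2355 to 2385.
- 25.9% and 94%: 2255 to 2284.
- 30% and 90%: 2033 to 2059.

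**The case against.** **The corner is pessimistic.** No single-dose albendazole or mebendazole cure rate quoted for *T. trichiura* exceeds 36%, so 45% vs 65% is an unlikely truth. This stands and limits the consequence. It does not remove the inconsistency, because the plan itself chose that corner to set its 105.

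**2000 may not be a cap.** Sample size says at least 2000, and Appendix 3 says to continue until 500–600 infected are found. The needed 549–556 lies inside that range, and 600 would give 115 per arm. This partly stands. But Field procedures and the ID numbering in Appendix 3 both run up to 2000, stopping at 500 is allowed, and at 25–25.9% prevalence the compliance figures above do not bring 2000 children to 500 infected.

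**30% may be attainable.** Two smears are read per baseline sample, and the number behind the 25.9% is not given, so comparability is unknown. This stands: 30% is unsupported rather than refuted. Field procedures nevertheless plans on 25%.

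**The losses may be overstated.** If exclusions and non-compliance before treatment overlap, fewer are lost. With only the 10% follow-up loss, 475 infected would leave 107 per arm. Some children randomised for other species may also prove positive for *T. trichiura* on the treatment day; their number is unknown. These points are fair, but the flowchart prints and deducts all three losses and no gain.

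**Stronger readings the documents do not support.** A reader might infer that the trial as a whole lacks 80% power; step 5 of the working shows otherwise. A reader might also take the yield down to 84 per arm, using 85% compliance with 25.9%. That 85% is a floor for giving one to three samples, while Study area and population surveyed reports 94% for at least one sample, so 89–93 is the better-supported range.

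**Conclusion.** The figures are wrong as written and need reconciling. The Field procedures inputs fall 65 infected children short of the stated 540 (475). The flowchart, on more favourable inputs, ends 2 per arm short of 105; the other stated inputs end about 12–16 short (89–93).

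The effect on power is modest and local. At 45% vs 65% it is about 79% at 103 per arm and 72–74% at 89–93 by the plan's formula, or about 84% and 78–80% without the correction terms. No test is named in the Data analysis section, so neither version can be called the only right one. At the remaining Table 1 combinations in the assumed range, power exceeds 80% even at 89 per arm.

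This rests on the flowchart's losses applying in full, on equal allocation to four arms, and, for the lower yields, on about 2000 children being approached.

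**What to change.** 1. Use one prevalence and one compliance figure in Field procedures, Sample size and Appendix 8. If 30% is kept for a one-sample, two-smear screen, give the evidence, including the number of smears behind the 25.9%.
2. Replace the 500–600 range by a single screening stop at about 549–556 infected children (105–106 evaluable per arm).
3. Restate the expected number screened: about 2310–2390 at 25% with 95% or 25.9% with 90% (about 2255–2285 if 94% compliance is adopted with 25.9%), or about 2030–2060 at a justified 30% with 90%. Confirm that the schools can supply it; the protocol gives 500–2000 pupils per school.
4. If 2000 is a hard cap, say so, and restate power at 45% vs 65% as about 72–74% by the plan's formula, noting that it exceeds 80% at the other Table 1 combinations in the assumed range.
5. Correct the flowchart's n = 100 to 200.

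The cost is edited text and either some 30–390 more children screened, depending on the inputs adopted, or a less favourable power statement for one contrast. The design and the planned 500–600 entrants are unchanged.

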## Laboratory procedures

All stool samples will be transferred to the HCLU on the day of collection, and will be examined by experienced laboratory technicians and the PhD-student. At the baseline screening, 2 Kato-Katz thick smears *(*41) from one stool sample per individual using 41.7 mg of stool will be prepared and examined quantitatively for the presence of hookworm eggs after a clearing time of 20-30 min, and subsequently for *A. lumbricoides* and *T. trichiura* eggs. The eggs of *A.* *lumbricoides*, hookworms and *T. trichiura* will be counted and recorded separately. From 250 randomly selected stool samples 1-2 g will be preserved in SAF for subsequent examination with the FLOTAC method *(*54).

From children included into the randomized controlled trial and thus providing another stool sample at the day of treatment and 2 consecutive stool samples for the follow up, a double Kato-Katz thick smear will be prepared and examined. At the days of follow up 1-2 g of stool, from those individuals examined with FLOTAC before treatment and who have been included in the trial, will again be preserved in SAF for subsequent examination with the FLOTAC method. All laboratory investigations will be blinded, e.g. the technicians examining the Kato-Katz slides or FLOTAC apparatus will not be aware of the treatment regimen of the participants. A random sample of 10% of the Kato-Katz thick smears will be re-examined by a Tanzanian senior laboratory technician for quality control.

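### Children are allocated before the exclusion check and the day-of-treatment stool, so the plan expects 15.6% per arm to leave between allocation and treatment, with no concealment described

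*Combined protocol and SAP*

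**What the plan says.** **Order of steps.** Field procedures: "Once all samples have been collected and analysed, a randomized treatment list allocating the IDs of the ~540 children infected with" *T. trichiura*, together with the remaining infected children, is prepared after the baseline reading. The text continues: "On the day before treatment the selected children will be given another stool container and they will be asked to provide another stool sample". Appendix 3 (weeks 5 and 6) lists random assignment to the four regimens, then the check for exclusion criteria, then the second stool container and its collection, then dosing.

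**Eligibility on the treatment day.** A day-of-treatment stool is inclusion criterion 3, and the first exclusion criterion is "No stool sample given at baseline survey or day of treatment". Other criteria carry the same timing: "Absence of major systemic illnesses, as assessed by medical personnel on the day of treatment", a verbal pregnancy check, and severe liver disorder "as assessed by medical personal with an abdominal examination on the day of treatment". One sentence in Field procedures is less definite: "Before the onset of the trial, each individual included into the trial will be physically examined by a medical assistant for exclusion criteria". It gives no date relative to the list.

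**Planned numbers.** Appendix 8 allocates 540 children, 135 per arm. Each arm shows 7 exclusions (5%) and 14 not complying (10%), 114 treated, 11 more not complying (10%), and 103 evaluable.

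**Who is analysed.** Study type and measurement defines the cure-rate total as children with stool from both day 0 and follow-up. Follow-up containers go to treated children only.

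**Masking.** Both single-drug arms receive a placebo resembling ivermectin. Blinding is stated for the laboratory: "the technicians examining the Kato-Katz slides or FLOTAC apparatus will not be aware of the treatment regimen of the participants". For clinical staff: "The medical assistant will be provided with a complete list of possible adverse events of the respective drug". The participation form in Appendix 5 carries each child's name, ID and uncoded regimen on one row.

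**The concern.** Randomisation protects a comparison only for the children who stay in it. Here a further selection step sits between allocation and first dose, and everyone it removes is lost to the efficacy analysis. Part of that step is judgement: signs of acute illness, major systemic illness, a verbal answer about pregnancy. If the person judging can learn the child's regimen from the list, exclusions can differ by arm without anyone intending it. The documents do not say who holds the list, how it is concealed, or whether the examining and dosing staff are blinded.

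A separate and smaller matter concerns safety. The safety of mebendazole plus ivermectin is a stated question of the trial. If acute events are recorded against a list that differs by drug, the events looked for may also differ by drug.

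**Working it through.** **1. Order, source by source.**
- Appendix 3: assign, check exclusions, second stool, dose. Explicit.
- Appendix 8: 135 allocated per arm, then 7 and 14 removed, then 114 treated. The chart survives only as text, but 135 − 7 − 14 = 114 fixes the position of these losses.
- Field procedures: list made after the baseline reading, second stool requested afterwards. Exam undated relative to the list.
- Inclusion and exclusion criteria: several checks on the treatment day, with no mention of allocation.

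Two sources place the exclusion check after allocation, and none clearly places it before.

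**2. The plan's own figures, per arm.**
- 5% × 135 = 6.75, shown as 7; 10% × 135 = 13.5, shown as 14; 135 − 7 − 14 = 114.
- 10% × 114 = 11.4, shown as 11; 114 − 11 = 103.

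All reproduce.

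**3. Loss after allocation.**
- Before treatment: (7 + 14)/135 = 15.6%; over four arms, 84 of 540.
- After treatment: 11/114 = 9.6%.
- In all: (21 + 11)/135 = 32/135 = 23.7%; over four arms, 128 of 540.

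**4. Possible distortion.** Let a fraction *f* of an arm be removed, and let the removed differ from the retained by *d* points in cure rate. The retained rate then differs from that of the full allocated arm by *f × d*. The documents give no value for *d*; I assume 20 points. The result is proportional to *d*, so 10 points would halve it.
- Staff exclusions only: 7/135 × 20 = 1.0 point.
- Exclusions and non-compliance: 21/135 × 20 = 3.1 points.

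These are errors in the comparison only if the selection acts in one arm. If it acts equally in all arms, they cancel in the difference. The smallest difference the trial is sized for is 20 points (45% against 65%).

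**5. After re-ordering.**
- Allocated: 4 × 114 = 456 in the *T. trichiura* stratum.
- Loss after randomisation: 11/114 = 9.6%, down from 23.7%.
- Evaluable: still 103 per arm.

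**6. Against the stated requirement.** The plan's formula at 45% and 65% gives 7.85 × (0.45 × 0.55 + 0.65 × 0.35)/0.20² + 2/0.20 + 2 = 105.2, the stated 105. The 103 is two short under either order. Reaching 105 takes 105 × 135/103 = 137.6, so 138 allocated per arm in the current order, or 105 × 114/103 = 116.2, so 117 per arm in the changed order.

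**The case against.** **The order is not uniform in the text.** In Field procedures the exam sentence stands before the paragraph on the list, and the statement that children will be allocated to four groups follows the treatment-day stool and weighing. A reader could take the exam to come first. This stands as an inconsistency to reconcile. It does not overturn the conclusion, because the list already ties IDs to regimens and Appendix 3 sets out the sequence step by step.

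**Late exclusion can be harmless.** If the examiner does not know the regimen and applies criteria that treatment cannot affect, removing ineligible children after allocation does not bias the comparison. The ivermectin placebo shows that masking was intended, and it covers the contrast on which the trial is sized. That is fair. A reader might infer that clinical staff know each child's arm; the documents do not show this. They are silent on concealment in the sections available, and the uncoded participation form leaves the question open.

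**Most of the loss is not a staff decision.** Of the 21, 14 are children not complying, and nothing says that they know their arm before dosing. This stands, and it is why about 1 point is the figure for staff exclusions and about 3 an upper case.

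**The event list acts later.** A reader might link the drug-specific list to the 15.6% loss. It cannot cause it, since the list belongs to the treatment phase. Nor does it expose all the safety data: solicited events use what appears to be one questionnaire for everyone. The wording may also mean one reference list per study drug rather than disclosure of a child's regimen. These points stand and confine the safety remark to acute events.

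**Conclusion.** The point holds as a weakness in the stated sequence that should be corrected before the trial starts. Allocation precedes the exclusion check and a stool sample on which eligibility depends, 15.6% per arm are expected to leave before treatment and 23.7% in all, and these children are not in the cure rate.

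What is shown is a risk of selection bias. A reader might infer that losses differ between arms, but the 5% and 10% are planning figures set equal in all four. The sizes of about 1 and 3 points rest on the assumed 20-point difference and on selection acting in one arm only. Either is small beside the planned 20-point difference, so the case for change rests on how cheaply the risk can be removed. Confidence is medium, because the order is not stated consistently and concealment may have been arranged without being written down.

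**What to change.** **Order.** On the treatment day, complete the exclusion exam and collect the second stool, then allocate only the eligible children present. The stool has to be received in sufficient quantity but need not be read first, since infection is defined at the baseline survey. Bring Field procedures, Appendix 3 and Appendix 8 into line with this order.

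**Concealment.** State who generates and holds the list, and keep it from the staff who examine children. Keep the *T. trichiura* list and the *A. lumbricoides*/hookworm list as separate strata. State whether examining and dosing staff are blinded.

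**Acute events.** Replace the list for the respective drug with one list common to all four regimens, and leave the regimen off the assessors' forms.

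**If the order cannot change**, record each eligibility decision before the child's allocation is revealed, and report exclusions by arm and reason.

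**Cost.** Allocation moves to the treatment day, with some added logistics; tablet numbers already depend on the weight taken that day. The 456 covers the *T. trichiura* stratum only, and the other stratum is extra. Coded packs would not by themselves mask albendazole from mebendazole, so the protocol should say plainly whether that contrast is blinded.
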